## Abstract

**Background:**

Cardiovascular disease (CVD) and cancer are the first and second causes of death in over 130 countries across the world. They are also among the top three causes in almost 180 countries worldwide. Cardiovascular complications are often noticed in cancer patients, with nearly 20% exhibiting cardiovascular comorbidities. Physical exercise may be helpful for cancer survivors and people living with cancer (PLWC), as it prevents relapses, CVD, and cardiotoxicity. Therefore, it is beneficial to recommend exercise as part of cardio-oncology preventive care.

**Objective:**

With the progress of deep learning algorithms and the improvement of big data processing techniques, artificial intelligence (AI) has gradually become popular in the fields of medicine and healthcare. In the context of the shortage of medical resources in China, it is of great significance to adopt AI and machine learning methods for prescription recommendations. This study aims to develop an interpretable machine learning-based intelligent system of exercise prescription for cardio-oncology preventive care, and this paper presents the study protocol.

**Methods:**

This will be a retrospective machine learning modeling cohort study with interventional methods (i.e., exercise prescription). We will recruit PLWC participants at baseline (from 1 January 2025 to 31 December 2026) and follow up over several years (from 1 January 2027 to 31 December 2028). Specifically, participants will be eligible if they are (1) PLWC in Stage I or cancer survivors from Stage I; (2) aged between 18 and 55 years; (3) interested in physical exercise for rehabilitation; (4) willing to wear smart sensors/watches; (5) assessed by doctors as suitable for exercise interventions. At baseline, clinical exercise physiologist certificated by the joint training program (from 1 January 2023 to 31 December 2024) of American College of Sports Medicine and Chinese Association of Sports Medicine will recommend exercise prescription to each participant. During the follow-up, effective exercise prescription will be determined by assessing the CVD status of the participants.

**Expected outcomes:**

This study aims to develop not only an interpretable machine learning model to recommend exercise prescription but also an intelligent system of exercise prescription for precision cardio-oncology preventive care.

**Ethics:**

This study is approved by Human Experimental Ethics Inspection of Guangzhou Sport University.

**Clinical trial registration:**

http://www.chictr.org.cn, identifier ChiCTR2300077887.

## 1 Introduction

Globally, cardiovascular disease (CVD) ranks as the first leading cause of death, while cancer ranks as the second in around 130 countries (1). These two factors are also among the top three killers in almost 180 countries worldwide (2). People living with cancer (PLWC) usually exhibit cardiovascular complications resulting from so-called “cardio-toxicity” (3) (which is defined as any heart damage arising from cancer treatments) as well as the overlap of risk factors of cancer and CVD, including an unbalanced fat diet, alcohol abuse, and physical inactivity (4).

Interventions using some common prevention strategies for these risk factors exist. For example, regularly engaging in physical activity (i.e., exercise prescription) is an efficient prevention strategy for cardio-oncology (5) because physical exercise can reduce not only cardio-toxicity but also the adverse effects of chemotherapy, including lymphoedema, fatigue, and immunological disorders (6). As a result, among PLWC or cancer survivors, physical exercise is a valuable tool for CVD prevention. Therefore, it is beneficial to recommend exercise prescription in cardio-oncology preventive care (5).

Artificial Intelligence (AI) has been widely employed in healthcare and medicine, especially since great advancements in deep learning algorithms and significant improvements to big data processing techniques (7). The fields of mental health (8), internal medicine (9), infectious diseases control (10), heart failure (11, 12), and diabetes (13), among others employ AI. In the context of the shortage of medical resources in China, developing prescription recommendation systems using AI and machine learning methods is promising (14). Wang et al. have proposed a reinforcement learning-based dynamic prescription recommendation system (15).

As for a dynamic recommendation system of exercise prescription, Tuka and Linhart discussed the possibility of utilizing AI and machine learning approaches for personalized exercise prescription recommendations for patients (16). More specifically, Chen et al. presented a hierarchical learning framework for Chinese kids’ physical exercise prescription (17). However, there is no existing studies have examined machine learning-based exercise prescription recommendations for cardio-oncology preventive care. Therefore, we aim to develop an interpretable machine learning-based intelligent system of exercise prescription for cardio-oncology preventive care and present the study protocol.

## 2 Methods and analysis

### 2.1 Design

This will be a cohort study with retrospective machine learning modeling. The study timeline is presented in Figure 1.

**FIGURE 1 F1:**
[figure not shown]
The timeline of this study.

From 1 January 2023 to 31 December 2024, we will train our exercise prescription doctors in the training program for clinical exercise physiologist (CEP). This training program is jointly supported by American College of Sports Medicine (ACSM) and Chinese Association of Sports Medicine (CASM). Candidates who are admitted to this training program should either hold a bachelor’s degree (or above) in medicine/public health or have at least 3-year professional clinical experience in healthcare. Additionally, candidates are supposed to have a vast knowledge of physical education and sports training as well. In this training program, candidates need to complete reading materials, online courses, offline tutorials, practice, and examinations. The offline training activities will take place at Zhuhai, China, where a certificated training base of ACSM-CASM CEP programs locates on. After completion of all modules, our exercise prescription doctors will be certificated jointly by ACSM and CASM as CEP. From 1 January 2025 to 31 December 2026, we will recruit 600 participants who are PLWC (in Stage I) or cancer survivors (from Stage I) for this study. The baseline characteristics including demographics, cancer-related information, exercise habits and lifestyle, health-related physical fitness, and CVD-related items will be collected based on physical examination or biomedical testing, where necessary. Then the exercise prescription doctors certificated by ACSM-CASM will recommend exercise prescription to each participant based on the abovementioned variables. During the 2-year exercise intervention period, we will monitor each participant’s completion status through wearable devices, which can record one’s physical activity every day. Additionally, our health management team will keep track of participants every week to ensure their adherence. We will undertake the follow-up study between 1 January 2027 and 31 December 2028, re-examining CVD-related items for all participants. Finally, effective exercise prescription will be assessed based on the changes in CVD-related items from the baseline to the follow-up, and interpretable machine learning models will be adopted in effective exercise prescription. The intelligent exercise prescription recommendation system will be developed based on some machine learning models with both good interpretability and high performance.

### 2.2 Selection of subjects

This protocol involving human participants was reviewed and approved by the Ethics Committee of Guangzhou Sport University. The participants will be provided with their written informed consent to participate in this study.

#### 2.2.1 Inclusion criteria

Participants will be eligible if they are (1) PLWC in Stage I or cancer survivors from Stage I; (2) aged between 18 and 55 years; (3) interested in physical exercise for rehabilitation; (4) willing to wear smart sensors/watches; (5) assessed by doctors as suitable for exercise interventions.

#### 2.2.2 Exclusion criteria

Participants will be ineligible for inclusion if they have: (1) current or recent serious sports injuries; or (2) existing severe CVD; or (3) other conditions that may not be suitable for exercise interventions, as assessed by doctors.

### 2.3 The sample size

We will recruit 600 participants for this study. Generally, the minimum sample size for machine learning modeling is 200 (18). We estimate the loss rate in the follow-up is 47% according to a finding that 53% cancer survivors do not follow the recommended physical activity guidelines (19). We infer that 65% of exercise prescriptions will be assessed as effective for cardio-oncology preventive care after the follow-up and used for machine learning modeling. This assumed value is based on the effectiveness rate of exercise prescriptions in reducing the risk of cardiovascular events among cancer patients (20). Therefore, at least 200÷65%÷53%=580.55 participants are needed. As a result, we decide to recruit 600 participants in the baseline to ensure the guarantee the minimum sample size for machine learning modeling at last.

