Some deep learning models will also be employed to evaluate the classification performance (accuracy, precision, recall, F-1 score, area under curve) in fivefold cross-validations, comparing them with the above-mentioned explainable machine learning models. Explanations of deep neural networks can be challenging (59), and hence to ensure that our deep learning models (convolutional neural networks, eXtreme gradient boosting, multilayer perceptron, deep residual network, DeepGBM) are more interpretable, an explainability tool named SHapley Additive exPlanations (SHAP), (60) will also be included. Recent advances in interpretability study for deep learning models have demonstrated the explainable potential for such models utilizing SHAP. For example, Zhao et al. proposed a novel SHAP scores computing algorithm for convolutional neural networks in classification (61). Meng et al. developed an integrated framework with better interpretability based on SHAP and eXtreme gradient boosting (62).

Since the intervention duration will be 2 years, there might be a great chance of loss-to-follow-up. Therefore, we set our sample size as 600 instead of 580, to cope with a higher loss rate or lower effectiveness rate than our initial estimations. If the final sample size for machine learning modeling still fails to reach the minimum bound (18), we will employ some few-shot learning algorithms (63) in such small size machine learning task to deal with this potential problem.

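### The sample-size section derives a 47% follow-up loss from a source rate worded as 53% not following guidelines; the two must be reconciled, because 600 recruits give about 207 or about 183 usable records depending on which is right

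*Protocol article*

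**What the plan says.** Section 2.3 of the protocol article sets a target of 200 records for modelling, taken from a general rule (reference 18), and inflates it for two losses.

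- **Follow-up loss:** "We estimate the loss rate in the follow-up is 47% according to a finding that 53% cancer survivors do not follow" the activity guidelines (reference 19).
- **Effective share:** "We infer that 65% of exercise prescriptions will be assessed as effective for cardio-oncology preventive care after the follow-up". Only these prescriptions enter the modelling.
- **Result:** "at least 200÷65%÷53%=580.55 participants are needed".

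The section then fixes recruitment at 600 and presents that number as securing the 200.

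Section 2.6 returns to the margin: "we set our sample size as 600 instead of 580, to cope with a higher loss rate or lower effectiveness rate" than first estimated. It adds that few-shot methods will be used if the modelling sample still falls below the minimum.

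**The concern.** The first input does not follow from its stated source. The sentence uses failure to follow activity guidelines as the proxy for loss to follow-up. A finding that 53% do not follow then implies 53% lost and 47% retained. The section takes 47% as lost and divides by 53%, so either the wording or the number is the wrong way round.

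This is the article's only justification of its sample size, and the whole calculation is printed there. The two readings fall on opposite sides of the 200-record target. On one of them, the few-shot methods that section 2.6 holds in reserve become the likely route to the recommendation model.

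**Working it through.** **Inputs, all from section 2.3:** minimum of 200 modelling records; effective share 0.65; retention 0.53 as used, or 0.47 if the 53% in the quoted finding is the loss; planned recruitment 600.

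**1. The plan's own figure.** Required N = 200 / effective share / retention.

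200 / 0.65 = 307.69, and 307.69 / 0.53 = 580.55. This reproduces the stated figure, so the division itself is right.

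**2. The same formula with the finding as worded.** 307.69 / 0.47 = 654.66, so 655 participants. This exceeds 600.

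**3. Expected usable records from 600 recruits.** Yield = 600 × retention × effective share.

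- Retention 0.53: 600 × 0.53 × 0.65 = 206.7.
- Retention 0.47: 600 × 0.47 × 0.65 = 183.3, which is 16.7 below 200.

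**4. Chance of reaching 200.** Treat each recruit as independently yielding a usable record with probability p = retention × effective share, so that the count is Binomial(600, p).

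- Retention 0.53: p = 0.3445, P(at least 200) = 0.731.
- Retention 0.47: p = 0.3055, P(at least 200) = 0.076.

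**5. What the step from 580 to 600 covers.** For 600 recruits to give 200 records on average:

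- With the effective share at 0.65, retention must be at least 200 / 600 / 0.65 = 0.513, so loss may be at most 48.7%. That is 1.7 percentage points above the assumed 47%, whereas the two readings differ by 6 points.
- With retention at 0.53, the effective share must be at least 200 / 600 / 0.53 = 0.629.
- With retention at 0.47, it must be at least 200 / 600 / 0.47 = 0.709, above the assumed 0.65.

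| Reading of the 53% | Loss | Retained | N required | Expected from 600 | P(at least 200) |
|---|---|---|---|---|---|
| Share following (wording is the slip) | 47% | 53% | 580.55 | 206.7 | 0.73 |
| Share not following (as worded) | 53% | 47% | 654.7 | 183.3 | 0.08 |

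**The case against.** The strongest reply is that the slip may be one of wording. The stated 47% loss and the division by 53% agree with each other; only the negative in the description of the finding conflicts with them. If reference 19 reports that 53% do follow the guidelines, a single stray word explains everything and 580.55 is sound on its assumptions. This stands. A reader might infer that the plan's own inputs yield only 183 records and that 655 is simply the correct number. The article does not support that outright: its declared input is a 47% loss, and the source is not at hand.

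A second reply is that neither percentage measures attrition. Not meeting activity guidelines is a proxy. Participants here must be interested in exercise and willing to wear devices (section 2.2.1), and they are followed weekly, pay a returnable deposit and receive equipment every 6 months (section 2.5). This also stands, so 47% retention should not be treated as the true figure. It does not remove the contradiction, since the section itself chose this proxy.

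A third reply is that section 2.6 already admits that 200 may be missed and names a fallback, and that any sample size based on an expected value can fall short. That softens the consequence. It does not justify section 2.3 in presenting 600 as securing the target.

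A reader might also infer that the 65% is wrong, because it is drawn from cardiovascular event risk while section 2.6 judges effectiveness on CVD-related items. The documents do not carry that far: section 2.3 openly labels the 65% an assumption, and the rule in section 2.6 is given only as an example. That point is not pressed.

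**Conclusion.** Section 2.3 contradicts itself and must be reconciled with its source. The direction of the error is open.

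If 53% is the share not following, 655 recruits are needed, and 600 fall about 17 records short on average with about an 8% chance of reaching 200. If 53% is the share following, the calculation stands and only the sentence is wrong.

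The assurance that 600 will deliver 200 fails either way, because even the favourable reading leaves about a 27% chance of missing the target. These figures rest on the plan's 65% effective share and its choice of proxy, and the probabilities also rest on independence between participants. No hypothesis test or power claim is affected.

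**What to change.** 1. Check reference 19 and correct section 2.3 so that the sentence and the division agree.
2. If 53% is the share **not** following: state loss 53%, retention 47% and a requirement of 200/0.65/0.47 = 655. If recruitment stays at 600, state that about 183 usable records are expected, that the chance of at least 200 is about 8%, and that the few-shot fallback in section 2.6 is the likely path.
3. If 53% is the share **following**: correct the wording and keep 580.55, with about 207 records expected.
4. In either case, replace the assurance in section 2.3 that 600 secures the minimum with the expected yield and the chance of reaching 200.
5. Bring the statement in section 2.6 about 600 against 580 into line. At a 65% effective share, 600 reaches 200 on average only if loss is at most 48.7%.

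The cost is wording in two sections and, on one reading, a less favourable stated yield. No further participants are needed unless the sponsor wants to hold the target of 200 under 53% loss. In that case 655 reaches it only on average (655 × 0.3055 = 200.1).

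### Recruiting 600 does not guarantee 200 modelling records: at the plan's own rates the chance is about 73%, and the cushion covers under 2 points of extra loss or about 2 points of lower effectiveness

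*Protocol article*

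**What the plan says.** Section 2.3 sets one size criterion: "Generally, the minimum sample size for machine learning modeling is 200". It assumes 47% loss to follow-up, so 53% retained. It also assumes a yield among those retained: "We infer that 65% of exercise prescriptions will be assessed as effective for cardio-oncology preventive care after the follow-up and used for machine learning modeling". From these it concludes that "at least 200÷65%÷53%=580.55 participants are needed", and then: "we decide to recruit 600 participants in the baseline to ensure the guarantee the minimum sample size for machine learning modeling at last".

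Section 2.6 returns to the choice of 600: "we set our sample size as 600 instead of 580, to cope with a higher loss rate or lower effectiveness rate than our initial estimations". The same paragraph warns that loss over two years may be considerable, and names few-shot learning as the fallback if the modelling sample is still under the minimum. Neither section gives a probability of reaching 200 or says how much worse the rates could be before 600 is too few.

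**The concern.** Dividing a required count by the expected proportions gives the recruitment at which that count is met on average. The number of usable records will vary around its expectation, so a study sized this way falls short nearly half the time even when its assumptions are right. Going from 581 to 600 adds 19 recruits, which is worth only about 6.5 expected records. Section 2.3 nevertheless treats the result as an assurance, and Section 2.6 treats the step up as protection against worse rates without giving its size.

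This matters because 200 is the only size criterion in the document and because missing it changes the modelling method. A reader who takes Section 2.3 at its word would give the fallback little weight.

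**Working it through.** **Inputs, all from Section 2.3:** minimum 200 records; retention 53% (loss 47%); effectiveness 65%; recruitment 600.

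**1. The plan's figure.** 200 / 0.65 / 0.53 = 580.55, that is 581 participants. It reproduces exactly.

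**2. What that figure delivers.** The chance that a recruit yields a usable record is 0.53 × 0.65 = 0.3445. If participants are independent and the rates are exact, the number of records X is Binomial(N, 0.3445).
- N = 581: expected 581 × 0.3445 = 200.2; exact P(X ≥ 200) = 0.521.
- N = 600: expected 600 × 0.3445 = 206.7; SD = √(600 × 0.3445 × 0.6555) = 11.6; exact P(X ≥ 200) = 0.731.

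The chance of a shortfall at 600 is therefore 1 − 0.731 = 0.269. The margin of 6.7 expected records over the minimum is less than one SD.

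**3. Size of the cushion.** These break-even rates make the expected yield at N = 600 equal to 200. They need no binomial assumption.
- Loss, effectiveness held at 65%: 1 − 200 / (600 × 0.65) = 1 − 200/390 = 48.7%, which is 1.7 points above plan.
- Effectiveness, loss held at 47%: 200 / (600 × 0.53) = 200/318 = 62.9%, which is 2.1 points below plan.

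At either break-even the chance of 200 records is only about one half.

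**4. Chance of at least 200 records at N = 600, one rate varied at a time.** The rates other than the plan's are illustrative.

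| Loss | Effective | Expected records | P(X ≥ 200) |
|---|---|---|---|
| 47% (plan) | 65% (plan) | 206.7 | 73% |
| 48% | 65% | 202.8 | 61% |
| 49% | 65% | 198.9 | 48% |
| 50% | 65% | 195.0 | 35% |
| 47% | 63% | 200.3 | 53% |
| 47% | 60% | 190.8 | 22% |

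**5. For scale.** At the plan's rates, the smallest N giving at least 200 records with 80%, 90%, 95% and 99% probability is 608, 624, 637 and 661. None of these is a guarantee either; they show how far 600 is from one.

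**The case against.** The best defence has four parts.

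- **The arithmetic is right, and the method is the ordinary attrition adjustment.** This stands. The fault lies in what the result is said to show, not in the calculation.
- **Section 2.6 already discloses the risk.** It foresees heavy loss and names a fallback, so the wording in Section 2.3 could be read as loose English for an aim. The disclosure does soften the consequence. It does not make the statement in Section 2.3 true, and it sits badly beside it.
- **The cushion is real.** This stands too. On expected counts, 600 does tolerate slightly worse rates, and Section 2.6 claims no particular size. The sentence needs a number; it need not be struck out as false.
- **The practical harm is limited.** The minimum is offered as a general rule. At the plan's rates there is a 95% chance of at least 188 records, and when the yield is under 200 it averages about 192. The documents show no sharp loss of quality between 192 and 200 records. What a miss does trigger is the plan's own change of method.

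A reader might go further and infer that a shortfall is the likely outcome. The documents do not support that: at the stated rates it has about a 27% chance, and it passes one half only if the rates are worse than assumed. A reader might also bring in the inconsistency over whether the cited 53% is retention or loss. That is a separate point, and nothing here depends on it.

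**Conclusion.** The point holds as a statement about assurance. The calculation in Section 2.3 fixes the expected yield, and 600 recruits give about 207 expected records and about a 73% chance of reaching 200, not a guarantee. The protection described in Section 2.6 exists but amounts to about 1.7 points of extra loss or 2.1 points of lower effectiveness, one at a time.

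The 73% rests on independent participants and on both rates being exactly as assumed. Uncertainty about the rates, or clustering of participants, would widen the spread, and neither would restore a guarantee.

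**What to change.** Keep 600 and change the wording in two places.

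- **Section 2.3:** remove the guarantee. Say that 580.55 makes the expected yield equal 200, and that 600 gives about 207 expected records and about a 73% chance of at least 200 at the stated rates, with the independence and fixed-rate assumptions noted.
- **Section 2.6:** state the tolerance, with the expected yield staying at 200 or more up to 48.7% loss or down to 62.9% effectiveness, the other rate held. Add the 50% loss (35%) and 60% effectiveness (22%) figures as illustrations. Describe the few-shot analysis as a realistic possibility, about one in four at the stated rates and more if the rates are worse.

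The cost is a few sentences and a less favourable stated assurance. No extra participants and no change of design are needed. The 47%/53% question should be settled separately, and these figures recalculated if it changes the retention rate.
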